## 2. Materials and Methods

### 2.1. Research Questions

The objectives of the study are as follows: What is the current status of Chinese SCAD patient’s participation in SDM?

What are the experiences of Chinese SCAD patient’s participation in SDM?

What are the factors influencing Chinese SCAD patients’ participation in SDM?

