### 2.4. Stage 1: Quantitative Study

#### 2.4.1. Sample

A convenience sampling method will be used to recruit participants. The study included 14 demographic and clinical characteristics and seven dimensions corresponding to five formative scales, with a total of 21 variables (Table 1). According to the sample estimation algorithm proposed by Kendall [24], the sample size is 10–20 times the number of variables, and the minimum sample size of this quantitative survey is 210. Moreover, considering 20% of the lost follow-up rate and invalid questionnaires, the final minimum sample size for the study is 252.

The inclusion criteria are as follows: (1) meets the diagnostic criteria of SCAD in the Guidelines for Diagnosis and Treatment of Stable Coronary Heart Disease [25]; (2) ≥18 years old; (3) signed informed consent.

The exclusion criteria are as follows: (1) patients with emergency admissions; (2) patients fully delegated to the family decision-maker; (3) patients with communication disorders; (4) diagnosed with mental illnesses; (5) pregnant patients; (6) patients with severe cardiac, liver, or renal dysfunction or critical illness.

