#### 2.4.3. Instruments

Data collection will be performed by using the following instruments:(1)General information questionnaire: Demographic and clinical characteristic data will be obtained by the general information questionnaire. Demographic characteristics will include age, sex, BMI, ethnicity, marital status, education level, average annual household income, place of residence, working conditions, medical payment method, drinking status, and smoking status. Clinical characteristics will include the duration of illness, the first time to be hospitalized for SCAD or not, the severity of angina, stent implantation or not, and the number of diseased coronary arteries.(2)Questionnaire for measuring patient views of involvement in myocardial infarction care [26]: This questionnaire was developed by Judith E, and translated by H. Shen [27]. Patient attitudes towards SDM will be measured by the patient involvement section of this scale, which consists of 6 items. The responses to each item are scored from 1 (Don’t agree at all) to 4 (Agree completely) with the total scores ranging from 6 to 24 points. A higher score indicates a more positive attitude towards SDM on the part of the patient. Cronbach’s α for the subscale is 0.82, indicating good internal consistency reliability.(3)Decision Self-Efficacy Scale (DSES) [28]: DSES was developed by Bunn et al., and translated by S.T. Wang et al. [29]. Decision self-efficacy is the “self-confidence or belief in one’s abilities in SDM”, and we will use DSES to assess the self-efficacy of participants towards SDM. The response options will be measured on the 5-point Likert scale (0 = not at all confident to 4 = very confident). On the advice of the original author, the total self-efficacy score is obtained by summing the 11 items and then multiplying them by 11/25. The total score ranges from 0 (not confident) to 100 (extremely confident). DESE demonstrated excellent reliability in the original study (Cronbach’s α = 0.899). The English version of DSES was translated into Chinese, back-translated, and cross-culturally adapted according to Brisin’s principles. The Chinese version of DSES consisted of 11 items. The content validity index of the Chinese version scale was 0.966. The Cronbach’s α coefficient was 0.918. The correlation coefficients between the scores of each item and the total score were 0.627–0.796 (all *p* < 0.01).(4)The Autonomy Preference Index (API) [30]: API was developed by Ende, and translated by Kim et al. [31]. The intention was assessed by 6 items using responses on the 5-point Likert scale (1 = “strongly disagree” to 5 = “strongly agree”). Because scoring for these items is reversed, a lower score indicates a greater intention. The internal consistency reliability of the subscale was excellent (Cronbach’s α = 0.82), and the test–retest reliability was 0.84.(5)The 9-item Shared Decision-Making Questionnaire (SDM-Q-9) [32]: SDM-Q-9 was developed by Kriston, and translated by B.H. Luo et al. [33]. The English version of SDM-Q-9 was translated into Chinese, back-translated, and cross-culturally adapted according to Brisin’s principles. The degree of the patient’s actual participation in SDM during treatment will be assessed by 9 items using answers on the 6-point Likert questionnaire ranging from 1 to 6 (“completely disagree” to “completely agree”). The SDM-Q-9 showed excellent validity and high acceptance, and internal consistency yielded a Cronbach’s α of 0.938 in the test sample. The initial author suggested that the original score × 20/9 be converted to 0–100 points for easy comparison. The total scores of 0–33, 34–66, and 67 and above indicated low, medium, and high levels of patient participation in shared decision making, respectively. Higher scores indicate a greater degree of patient participation in SDM.(6)The Multidimensional Scale of Perceived Social Support [34]: MSPSS was developed by Zimet, and translated by Kee-Lee Chou [35]. Perceived social support was measured with the MSPSS. The scale consists of 12 items (Cronbach’s α = 0.89) with answers ranging from “Completely disagree” to “Completely agree” (1 to 7). The measure assesses social support received from three subscales (4 items each)—friend subscales (Cronbach’s α = 0.95), family subscales (Cronbach’s α = 0.92), and significant other subscales (Cronbach’s α = 0.91). The general scores were calculated by adding the 12 items together (ranging from 12 to 84). A higher total score indicates higher levels of social support for patients.

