
#### 2.4.4. Data Analysis

The questionnaire will be checked by two people, and scientific statistical methods will be used for rigorous statistical analysis. The quantitative data collected through interviews will be analyzed using SPSS26.0. Descriptive statistics will be used to present all the variables (Table 1). Mann–Whitney U-tests or multi-sample rank-sum tests will be used to analyze the differences between general information and the level of participation in SDM in patients with SCAD. The variables that are statistically significant after monofactor analysis will be used as independent variables, and participation in SDM by SCAD patients will be used as the dependent variable for conducting multiple logistic regression analyses. The Spearman correlation analysis will be used to describe the correlation between the variables in the TPB model and participation in SDM by SCAD patients. Two-tailed *p*-values will be adopted, and *p* < 0.05 will be considered statistically significant.

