### 3.2. Limitations

Firstly, our study participants will be recruited using convenience sampling from just one clinical setting. The single setting and the sampling methodology are non-probabilistic, limiting the findings’ generalizability. Secondly, for the elderly with lower levels of education, there is a possibility that they may not be able to comprehend the content of the questionnaires and interview outlines, which could potentially lead to communication difficulties. It is incumbent upon the researcher to elucidate the questionnaire and interview outline to the elderly in simple and clear statements. This may require a greater investment of time and energy on the part of the patient, which could potentially impede the research process.

TPB also has some limitations that should be mentioned. Firstly, TPB assumes that individuals make decisions based on the rational assessments of available information. In reality, however, people often make decisions based on past behavior and habits, which are not fully captured by the theory [39]. This may lead to overestimating the predictive power of attitudes, subjective norms, and perceived behavioral control in some situations. Secondly, TPB assumes that individuals have a degree of control over their behavior. However, in some cases, people may have limited control due to factors such as their medical condition, mental health problems, or environmental constraints. When patients lack control over their behavior, TPB’s predictive power is reduced because intentions may not be translated into action [39].

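### Excluding patients who fully delegate to family removes a form of non-participation by rule, while the research questions cover SCAD patients generally and the limitations do not mention it

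*Protocol article*

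**What the plan says.** All references are to the protocol article.

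- **Eligibility (2.4.1):** the second exclusion criterion is "patients fully delegated to the family decision-maker". No reason is given. Separate criteria remove emergency admissions, communication disorders, mental illness, and severe organ dysfunction or critical illness.
- **Target population (2.1):** question 1 begins "What is the current status of Chinese SCAD patient" and asks about participation in SDM. Question 3 is "What are the factors influencing Chinese SCAD patients’ participation in SDM". Neither is limited to patients who kept a role in the decision.
- **Outcome (2.4.3):** the SDM-Q-9 is the measure; the patient's "actual participation in SDM during treatment will be assessed by 9 items". It is then banded: "The total scores of 0–33, 34–66, and 67 and above indicated low, medium, and high levels of patient participation".
- **Analysis (2.4.4):** "participation in SDM by SCAD patients will be used as the dependent variable" in the logistic regression.
- **Limitations (3.2):** on sampling, the text says "The single setting and the sampling methodology are non-probabilistic, limiting the findings’ generalizability". The delegation criterion is not mentioned.

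**The concern.** The criterion selects patients on something very close to the dependent variable. Someone who hands the whole decision to family has, on the ordinary meaning of the words, not taken part in it. Removing such patients while describing participation in SCAD patients at large would tend to make participation look higher than it is. A larger sample does not correct this.

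The factors question is exposed too. Section 2.2 defines subjective norm through the pressure and support of significant others, and Table 2 asks interviewees how family affected their participation. Patients whose family took over the decision entirely are absent from the survey. Because interviewees come from the survey sample (2.5.1), they are absent from the second stage as well.

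What is at stake is the population to which the status figure and the list of influencing factors apply. A reader of the limitations would learn about the single site and the convenience sample, but not that one kind of non-participant was removed by rule.

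**Working it through.** The article gives no figure on this point, so there is none to reproduce. The size can only be set out as a formula and illustrated.

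**Inputs**
- d, the share of otherwise eligible patients who fully delegate: not in the document. Assumed 2% to 30%.
- p, the share in the low band (0–33) among those surveyed: not in the document. Assumed 10% to 40%.
- n = 210, the minimum before the loss allowance (2.4.1: 10 × 21 variables). It is used only to compare the shift with sampling error.

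**Low share**

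If every delegating patient counts as low, the low share among all otherwise eligible patients is d + (1 − d) × p. The survey reports p. The understatement is therefore d + (1 − d)p − p = d × (1 − p).

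Understatement in percentage points:

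| d | p = 10% | p = 20% | p = 30% | p = 40% |
|---|---|---|---|---|
| 2% | 1.8 | 1.6 | 1.4 | 1.2 |
| 5% | 4.5 | 4.0 | 3.5 | 3.0 |
| 10% | 9 | 8 | 7 | 6 |
| 20% | 18 | 16 | 14 | 12 |
| 30% | 27 | 24 | 21 | 18 |
| 95% half-width, n = 210 | 4.1 | 5.4 | 6.2 | 6.6 |

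The last row is 1.96 × √(p(1 − p)/210). Example: d = 10% and p = 30% give 0.10 + 0.90 × 0.30 = 37%, against 30% reported.

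The shift exceeds the half-width once d > half-width/(1 − p). At p = 10% that is 4.1/0.90, about 4.5%. At p = 30% it is 6.2/0.70, about 9%. Below those shares the shift is smaller than sampling error.

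**Mean score**

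The overstatement is d × (mean of surveyed − mean of delegating). It is positive only if delegating patients would score lower. With d from 5% to 30%, surveyed means of 50 to 70 and delegating means of 0 to 33 (all assumed, on the 0–100 scale that the article states), it runs from 0.05 × (50 − 33) = 0.85, about 0.9 points, to 0.30 × (70 − 0) = 21 points. With d = 10% and means of 60 and 20 it is 4 points.

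**Associations**

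No calculation is possible. The effect on the Spearman and logistic results depends on how delegation relates to each predictor, and the document gives nothing on that.

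**The case against.** The strongest case on the other side has five parts.

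1. **The reason for the criterion is not stated, and a sensible one may exist.** The Introduction says guidelines recommend SDM for patients capable of autonomous decisions, and section 3.2 notes that the theory of planned behavior predicts less well where people lack control. A condensed article may omit such reasons. The other exclusions also do not name cognitive impairment or formal surrogate authority, which this one might cover. This stands: a reader might infer that everyone excluded was able to take part and chose not to, but the text does not establish that. A good reason for the criterion would still not widen the population that the results describe.

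2. **The low end of the scale is not removed.** Patients scoring 0–33 who did not fully delegate stay eligible, and low participators are to be interviewed. This stands. A reader might infer that the outcome is cut off at the bottom; only one route to low participation is closed.

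3. **Direction and size are unproven.** This stands. The direction follows from the meaning of full delegation, not from data. Every value in the table is an assumption, and at d of 1–2% the shift is under 2 points.

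4. **Weaker associations are not demonstrated.** A reader might infer that links with self-efficacy, intention and family influence must be attenuated. Range restriction often does that, but here only possible distortion can be claimed.

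5. **Deleting the criterion is not clearly better.** The SDM-Q-9 may have little to rate where the patient was not the decision-maker. Section 2.4.2 also has offspring fill in the form for elderly patients with little education, so the relative who decided could be completing it. This stands and is why deletion is not recommended.

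The general caveat in 3.2 does not answer the point. A single site and convenience sampling say nothing about removing patients by how they took part.

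**Conclusion.** The point holds as a mismatch between eligibility and stated scope. The criterion removes a group closely tied to the outcome, questions 1 and 3 do not reflect that, and the limitations do not disclose it. If delegating patients would score below those enrolled, participation is overstated and the low share understated for the population named. That condition is likely but not shown.

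The size cannot be derived from the document. It is d × (1 − p) for the low share if all delegators count as low: 1.2 to 27 percentage points over the assumed ranges, and 7 points at d = 10%, p = 30%. Associations with family influence, intention and self-efficacy may be distorted, in a direction and amount unknown.

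The documents do not support saying that the criterion is wrong in itself or that a bias of a given size is established. For the narrower group of patients who did not fully delegate, the exclusion creates no such bias.

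**What to change.** The criterion may stay if the sponsor wishes. Then:

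- Record on the screening log how many approached, otherwise eligible patients are excluded for full delegation to family.
- Report that share as a separate category (fully delegated, not surveyed) beside the low, medium and high SDM-Q-9 distribution. Do not merge it into the measured bands in the main result.
- Add one sensitivity line that counts these patients as low participation, labelled as an assumption because they have no SDM-Q-9 score.
- Reword research questions 1 and 3 and the conclusions to cover patients who did not fully delegate, and name the exclusion in 3.2.

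The cost is a small screening tally, one or two lines of results, and a narrower stated conclusion. Under convenience sampling the denominator is only the patients approached, so the reported share describes them and does not estimate delegation in SCAD patients at large. The tally should be kept from the start of recruitment, because the count may not be recoverable later.

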#### 2.4.2. Study Setting and Data Collection

The study will be conducted at the Affiliated Hospital of Hangzhou Normal University in Hangzhou, Zhejiang Province, China.

Before the questionnaire survey, team members will receive unified training to master the purpose, method, content, and process of the questionnaire survey. When answering questions from patients, unified guidance language should be used to ensure the authenticity of answers and the reliability of data. With the support and cooperation of hospital staff and the consent of SCAD patients, investigators will require the participants to sign informed consent forms and provide their telephone numbers through which they can be contacted for the next stage. We will be preparing small gifts for patients to stimulate their enthusiasm to participate in the survey.

Data collection stage: One or two days before discharge, the researchers and participants will conduct face-to-face paper-and-pencil surveys to fill out questionnaires. The questionnaire survey will take about 10–15 min. For elderly patients with low educational levels, the researchers will clearly explain the contents of each survey and then ask the offspring of the patients to fill in the questionnaires. The questionnaires will be issued on the spot, and the questionnaires will be collected on the spot and checked in time to ensure the completeness and effectiveness of data collection.

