**Figure 3 healthcare-12-01883-f003:**
[figure not shown]
Gantt chart for this mixed method study.

**Table 1 healthcare-12-01883-t001:** Statistical test information table.

Statistical Test Information Table			
Num	Tests	Variables	Type of Information
1	descriptive statistics	demographic and clinical characteristics, participation in SDM, patient attitudes, decision self-efficacy, intention, and social support	Frequency, percentage; Mean ± SD or M (P_25_, P_75_) (normality or not)
2	monofactor analysis	sex, BMI, ethnicity, place of residence, working conditions, medical payment method, stent implantation or not, and the first time to be hospitalized for SCAD or not	Mann–Whitney U-tests
		age, marital status, education level, average annual household income, drinking status, smoking status, duration of illness, severity of angina, and number of diseased coronary arteries	multi-sample rank-sum tests
3	multiple logistic regression analyses	Variables that are statistically significant after monofactor analysis	independent variables
		participation in SDM	dependent variable
4	Spearman correlation analysis	participation in SDM (Single dimension)	
		patient attitudes (Single dimension)	
		decision self-efficacy (Single dimension)	
		intention (Single dimension)	
		social support (friends support, family support, and significant other support)	

Demographic and clinical characteristics: sex, BMI, ethnicity, place of residence, working conditions, medical payment method, stent implantation or not, and the first time to be hospitalized for SCAD or not; age, marital status, education level, average annual household income, drinking status, smoking status, duration of illness, severity of angina, and number of diseased coronary arteries.

**Table 2 healthcare-12-01883-t002:** Semi-structured Interview Outline.

Opening remarks	I appreciate your interest in this study. I will ask you some questions about your involvement in SDM during this hospitalization. Your responses will be recorded, but your identity will remain confidential.	

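### Offspring fill in the questionnaires for elderly, low-education patients, so the SDM-Q-9 outcome may change respondent with the two factors tested against it

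*Protocol article*

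**What the plan says.** The general procedure in section 2.4.2 of the protocol article is that "the researchers and participants will conduct face-to-face paper-and-pencil surveys to fill out questionnaires". One group, described as "For elderly patients with low educational levels", is handled differently. In that group the researchers first go through what each instrument contains, and their next step is to "ask the offspring of the patients to fill in the questionnaires". No age or education cut-off is given for this group.

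The pack described in section 2.4.3 holds scales for the patient's attitude, decision self-efficacy, intention and perceived social support (MSPSS, which has a family subscale). It also holds SDM-Q-9, which measures how far the patient actually took part in decisions.

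Section 2.4.4 uses rank-sum tests to "analyze the differences between general information and the level of participation in SDM in patients with SCAD". Table 1 names the variables for the multi-sample version of these tests, and the list begins with "age, marital status, education level". Variables that are significant go into the logistic regression of SDM participation. The theory-of-planned-behavior (TPB) scales are related to SDM participation by Spearman correlation.

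Section 3.2 recognises a related difficulty: "for the elderly with lower levels of education, there is a possibility that they may not be able to comprehend the content". It answers this with simpler explanation by the researcher and does not mention offspring completing the form.

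**The concern.** The person completing the form appears to change in a subgroup defined by age and education together, and the plan then tests age and education as factors. If offspring see the patient's involvement differently from the patient, that difference enters the comparison of elderly with younger patients and of low with higher education. It cannot be told apart from a true effect. It could also run against a true effect and hide it. A larger sample does not remove a bias of this kind.

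Two further problems follow from the same step:

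- **Spearman analyses.** If one offspring answers both the TPB scales and SDM-Q-9, the two sets of answers share a rater. That can add correlation which does not reflect the patient's own attitude, confidence or intention.
- **Family support.** The offspring belongs to the family being rated on the MSPSS family subscale.

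The factors that influence participation are one of the three research questions in section 2.1, so this bears on a core aim.

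**Working it through.** **1. Who answers, and what is tested.**

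| Element | Source | Content |
|---|---|---|
| Respondent, most patients | Section 2.4.2 | Participant, face to face with the researcher |
| Respondent, elderly and low education | Section 2.4.2 | Offspring fill in the form after an explanation |
| Outcome of the age and education tests | Section 2.4.4, Table 1 | SDM participation (SDM-Q-9) |
| Use of the TPB scales | Section 2.4.4, Table 1 | Spearman correlation with SDM participation |

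So the age and education tests are exposed through SDM-Q-9. Attitude, intention, self-efficacy and support are not tested against age or education. Their exposure is in the correlations.

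**2. Size of a spurious difference.** The plan states no figure on this point, so there is none to reproduce. The inputs below are assumptions:

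- *a* = share of the sample that is elderly = 0.50
- *e* = share with low education = 0.40
- *p* = share of all forms completed by offspring, all of them in patients who are both elderly and of low education
- *d* = mean shift of offspring-reported against patient-reported SDM-Q-9, in points on the 0–100 scale

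Suppose there is no true effect. The elderly group's mean moves by *d* × *p*/*a* and the younger group's mean does not move. The low-education group's mean moves by *d* × *p*/*e*.

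| *p* | Age, *d* = 10 | Education, *d* = 10 | Age, *d* = 5 | Education, *d* = 5 |
|---|---|---|---|---|
| 10% | 10 × 0.10/0.50 = 2 | 10 × 0.10/0.40 = 2.5 | 1 | 1.25 |
| 20% | 10 × 0.20/0.50 = 4 | 10 × 0.20/0.40 = 5 | 2 | 2.5 |
| 30% | 10 × 0.30/0.50 = 6 | 10 × 0.30/0.40 = 7.5 | 3 | 3.75 |

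The direction of *d* is unknown, so the difference could have either sign.

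**3. Effect on false-positive rates.** This was simulated with n = 210, the plan's minimum before inflation (10 × 21 variables). The test was a two-sided Mann–Whitney test at 0.05, with 3000 runs, no true effect, and the same 50% and 40% margins. The shift is in SD units and applies only to the elderly, low-education group.

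| *p* | Shift | Education test | Age test |
|---|---|---|---|
| 10% | 0.3 SD | 8% | 7% |
| 10% | 0.5 SD | 14% | 11% |
| 20% | 0.3 SD | 19% | 13% |
| 20% | 0.5 SD | 40% | 28% |
| 30% | 0.3 SD | 34% | 23% |
| 30% | 0.5 SD | 71% | 56% |

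With no shift, all rates stayed between 4.5% and 5.1%. The simulation splits age and education into two groups each, whereas the plan uses multi-sample rank-sum tests for both. It therefore shows the order of magnitude and does not predict this study's error rate.

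**The case against.** The strongest objection is that filling in the form may mean only writing down what the patient says. Some of the text supports this. Section 2.4.2 provides standard wording for answering patients' questions. Section 3.2 has the researcher explain the questionnaire to the elderly and counts the patient's own time and effort. Section 2.4.1 excludes patients with communication disorders and those who leave decisions entirely to the family. A reader might nevertheless take offspring reporting as established, and the article does not go that far. What stands is that it never says the offspring act as scribes, and the natural reading of the instruction is that they answer. The exclusion does not settle it either, because elderly, low-education patients who have not fully delegated remain eligible.

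Other stronger readings are tempting and should be resisted:

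- **That offspring-reported attitude, intention, self-efficacy and family support distort the age and education tests.** Those tests use SDM participation only.
- **That a 10-point shift appears in full as a 10-point age or education effect.** That would need a comparison of offspring-completed forms with all others. The planned tests take age and education separately, which dilutes the shift as shown above.
- **That family-support scores are biased upwards.** The article gives no evidence of direction.
- **That failing to mention completion mode is itself an error.** A condensed article may leave form fields and sensitivity analyses to the full protocol or SAP. The point rests on the procedure that is stated.

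**Conclusion.** The point holds as a conditional one. Section 2.4.2 sets out a procedure that, on its natural reading, lets the respondent for SDM-Q-9 change with age and education, the same variables then tested against it. Neither the exclusion criteria nor the stated limitation on comprehension removes this.

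The size cannot be known from the article. For a 10-point shift and the assumed margins, the spurious difference runs from 2 (age) and 2.5 (education) points at a 10% share to 6 and 7.5 points at 30%. At the low end (10% share, 0.3 SD) the false-positive rate barely moves, to 7–8%, while at larger shares and shifts it becomes serious. If offspring only transcribe the patient's answers, most of the concern falls away, though a family member is still present while family support is rated. The change is worth making because it is cheap before data collection and cannot be made afterwards.

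**What to change.** In section 2.4.2, replace the offspring step. The trained researcher, who is already present face to face, reads the items aloud and marks the patient's own answers, without input from offspring. Record completion mode on each form as self, researcher-read or offspring.

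Keep any unavoidable offspring-completed forms in the main analysis, and report a sensitivity analysis that adjusts for mode or leaves them out. Dropping them from the main analysis would selectively remove elderly, low-education patients. It could also be costly in numbers: at an assumed 30% share, 0.30 × 252 ≈ 76 forms would go, leaving about 176 against the plan's minimum of 210.

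The cost is some extra researcher minutes for each affected patient (section 2.4.2 puts the whole survey at 10–15 minutes) and one extra field on the form. A smaller mode difference, researcher-read against self-completed, would remain tied to age and education, but the recorded mode lets the analysis examine it. If the intention was always that offspring only transcribe, section 2.4.2 should say so, and mode should still be recorded.

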### 2.5. Stage 2: Qualitative Study

#### 2.5.1. Sample

To obtain as much information as possible from the interviews, maximum difference sampling will be used. The SCAD patients included in the quantitative study as the target population, and as far as possible, SCAD patients with different levels of SDM participation, with different risk factors for cardiovascular disease, with different ages, with different levels of education, and with different economic statuses representative of the results of the quantitative study will be selected for the interviews. The final sample size will be determined according to the information saturation; that is, the interview will end when no new content and themes emerge, and 10–20 interviewees are expected to be included.

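### Inpatients rate their own participation face to face and hand the form back for an on-the-spot check, which can push SDM-Q-9 scores upward; a sealed return costs almost nothing

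*Protocol article*

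**What the plan says.** Section 2.4.2 of the protocol article fixes the collection procedure for stage 1:

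- Timing and mode: "One or two days before discharge, the researchers and participants will conduct face-to-face paper-and-pencil surveys to fill out questionnaires". The respondent is still an inpatient and a researcher is present. Section 2.4.4 describes the quantitative data as gathered by interview.
- Access: the survey runs "With the support and cooperation of hospital staff and the consent of SCAD patients".
- Return: "the questionnaires will be collected on the spot and checked in time to ensure the completeness and effectiveness of data collection".
- Contact data: participants sign consent and "provide their telephone numbers through which they can be contacted for the next stage".
- Incentive: "We will be preparing small gifts for patients to stimulate their enthusiasm to participate in the survey".
- Stated aid to truthful answers: when patients ask questions, "unified guidance language should be used to ensure the authenticity of answers and the reliability of data".

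Section 2.5.1 then draws interviewees from the survey, seeking "SCAD patients with different levels of SDM participation, with different risk factors for cardiovascular disease". The only assurance of confidentiality in the article is in the opening remarks of the stage 2 interview (Table 2): "Your responses will be recorded, but your identity will remain confidential". Section 3.2 lists convenience sampling at a single site, comprehension problems in elderly patients with little schooling, and limits of the theory. It does not list response bias.

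**The concern.** The introduction describes shared decision making as a partnership in which provider and patient carry the decision together. The SDM-Q-9 asks how far that happened during the current treatment. A low rating can therefore be taken as a comment on the team that is still looking after the patient. Under the described procedure, the patient gives that rating with a researcher present and returns the form there and then for checking. Standardised wording makes researchers behave alike, but it does not give the patient privacy. Some patients may answer more favourably than they would in private.

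Two uses of the score are exposed. The first research question asks for the current level of participation, and a general upward shift biases that directly. The low, medium and high bands also guide the choice of interviewees, and the shift thins the low band. The introduction expects participation to be low, so the likely direction of the bias would hide what the study sets out to describe. A larger sample would not remove it.

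**Working it through.** The documents contain no estimate of this bias, so there is no figure to reproduce. The check has two parts.

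**1. What the text supports**

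| Element | Status |
|---|---|
| Completed in hospital, 1–2 days before discharge | Stated, 2.4.2 |
| Researcher present | Stated, 2.4.2 |
| Form returned and checked on the spot | Stated, 2.4.2 |
| Scores linkable to persons | Follows from 2.5.1 (selection by level of participation) and the telephone number in 2.4.2 |
| Name or telephone number on the questionnaire | Not stated |
| Answers read in front of the patient, or seen by treating staff | Not stated |

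**2. How sensitive the bands are (illustration only)**

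Inputs from section 2.4.3: 9 items; conversion by 20/9; low 0–33, medium 34–66, high 67 and above. Input from section 2.4.1: 210 patients before inflation. Assumed: a normal distribution on the 0–100 scale that the bands presuppose, means 40–60, SDs 15–25, and the same shift for everyone. (Items coded 1–6 and multiplied by 20/9 would run from 20 to 120. That is a separate matter and does not change the size of a shift.)

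A shift of s points per item moves the converted score by 9 × s × 20/9 = 20 × s. So 0.25, 0.5 and 1 point per item give 5, 10 and 20 points, against a medium band about 33 points wide.

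With m the shifted mean:

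- share high = 1 − Φ((66.5 − m)/SD)
- share low = Φ((33.5 − m)/SD)

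For mean 50 and SD 20:

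| Shift (converted) | High | Low | Low scorers in 210 |
|---|---|---|---|
| 0 | 20.5% | 20.5% | 43 |
| 5 | 28.3% | 14.1% | 30 |
| 10 | 37.3% | 9.3% | 20 |
| 20 | 56.9% | 3.4% | 7 |

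Example: with a 5-point shift, (66.5 − 55)/20 = 0.575, and 1 − Φ(0.575) = 0.283.

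Over all nine combinations of mean (40, 50, 60) and SD (15, 20, 25):

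- 5-point shift: high rises by 3.7 points (3.9% to 7.6%; mean 40, SD 15) to 12.8 points (33.2% to 46.0%; mean 60, SD 15). Low falls by 2.1 points (3.9% to 1.8%; mean 60, SD 15) to 11.0 points (33.2% to 22.2%; mean 40, SD 15).
- 10-point shift: high rises by 9.7 to 26.0 points.

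The 95% half-width for the mean at n = 210 is 1.96 × SD/√210, which is 2.0, 2.7 and 3.4 points for SDs of 15, 20 and 25. A 5-point shift would exceed it in each case.

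**Associations.** Adding the same amount to every score leaves the ranks unchanged apart from ties at the ceiling. The Spearman correlations, and rank tests on the score, would be largely unaffected. They are distorted only if courtesy answering varies with patient characteristics, or also affects the other scales filled in at the same sitting.

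**The case against.** The strongest reply is that much of this is inference from a condensed article. Contact details are collected at the consent step, and the questionnaire contents in section 2.4.3 include neither name nor telephone number. A study number would serve stage 2 equally well and may already be planned. Section 2.4.2 distinguishes researchers from hospital staff, whose part is support. The check has a stated purpose of completeness, confidentiality wording normally sits in the consent form, and completion in hospital avoids recall problems and loss of respondents.

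Most of that stands, and it limits the point. A reader might infer that the form carries the patient's identity, that answers are inspected in front of the patient, or that clinicians see them; the article says none of these. A reader might also infer that the low band would be emptied. It shrinks: in the mean-50 illustration, a 5-point shift still leaves about 30 low scorers, against 10–20 interviews planned in total. Nor do the documents support false differences by age or education. Section 2.4.2 does have offspring fill in forms for elderly patients with little schooling, so conditions differ between patients, but nothing shows that courtesy answering differs as a result.

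The reply does not remove the stated procedure. Timing, a researcher's presence, and on-the-spot return and checking are given in the text, so the point does not rest on silence alone. The purpose of the check also goes beyond completeness to an undefined effectiveness.

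**Conclusion.** The point holds as a cheap improvement to a stated collection step. The setting can bias the level of participation upward and thin the low band. Neither the existence nor the size of the bias can be shown from the documents, so the figures above show only how sensitive the bands would be. Under the assumed distributions, a quarter point per item would raise the high share by about 4 to 13 percentage points and lower the low share by about 2 to 11. The research question on the current level carries the main risk. The research question on influencing factors is affected only under the further assumption that courtesy answering differs between patients or extends to the other scales. There is no error of calculation or contradiction here.

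**What to change.** In section 2.4.2:

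- limit the on-the-spot check to blank items;
- have the patient then seal the form, bearing only a study number, in an envelope;
- keep consent and telephone number on a separate linked sheet, if this is not already done;
- add to the unified guidance script that treating staff will not see individual answers.

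In section 3.2, name residual social-desirability bias as a limitation, since the rating is still given in hospital with a researcher present.

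The cost is envelopes, a contact sheet and a sentence or two in the training script. The link to stage 2 and the check for missing items are both kept. The one downside is that implausible answers come to light only at data entry.
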